### **Results**

Baseline characteristics were analyzed using propensity score matching. A total of 164 patients were included, with 89 assigned to the multidimensional digital CR intervention group and 75 to the usual care group. After applying a 1:1 matching approach to adjust for baseline inconsistencies, 68 patients were selected from each

group. Statistically, non-significant differences were observed between the two groups after matching baseline data ( $P \geq 0.05$ ). Among 136 patients undergoing PCI (mean age: 70.0 years), 59 (43.38%) were female.

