159 research team will ensure that patients have signed the informed consent form before  
160 entering the study and will provide ongoing support and guidance throughout the  
161 study.

162 After the recruitment and pre-screening processes, patients were divided into two  
163 groups based on their admission dates: the control group (April to May 2022) and the  
164 intervention group (May to June 2022). In addition to receiving standardized  
165 treatment, the intervention group also received a multidimensional digital cardiac  
166 rehabilitation intervention, which encompassed seven dimensions: exercise training,  
167 medication management, nutritional guidance, psychological support, sleep  
168 management, health education, and smoking cessation support. It is important to note  
169 that, in addition to the intervention for patients themselves, the digital cardiac  
170 rehabilitation intervention particularly emphasized the involvement of the patients'  
171 family members. During the hospitalization period, family members were invited to  
172 participate in the rehabilitation training program, ensuring that they could provide

necessary support for the patients and promote health education within the home environment. The control group, on the other hand, received only standardized treatment and standard nursing care.

After the PCI procedure, both groups of patients underwent a three-month follow-up period. The follow-up included individualized educational sessions conducted monthly via the WeChat platform, in addition to outpatient visits at one and three months post-surgery. During the follow-up, patients were required to report their health status to the multidisciplinary intervention team, including blood pressure, physical activity, dietary habits, sleep patterns, psychological state, and progress in smoking cessation.

Only patients who completed all data collection requirements were included in the final analysis. The final dataset was subjected to propensity score matching to balance the baseline characteristics between the two groups, ensuring comparability.

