### **Randomization**

Owing to the nature of the intervention, the participants were not randomly assigned. To minimize potential confounding factors, the multidimensional digital cardiac rehabilitation intervention group and the usual care group were matched on the basis of propensity scores calculated using logistic multiple regression analysis. The matching process involved considering covariates such as age, sex, education level, marital status, exercise habits, monthly salary, current address, living arrangement

(solitary or not), history of CHD, history of PCI, length of hospitalization, medical insurance status and polypharmacy data obtained from presurveys. Propensity score analysis was conducted using a 1-to-1 ratio matching approach with the nearest neighbour method to ensure balanced characteristics between the intervention and control groups. A standard calliper width of 0.2 was used for the propensity score. After matching, a total of 136 patients were included, with 68 patients in the multidimensional digital cardiac rehabilitation group and 68 patients in the usual care group.

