### **Statistical Method**

Statistical analysis was performed using R (4.2.0). Continuous variables are presented as the means  $\pm$  standard deviations if they followed a normal distribution, and differences between groups were assessed via t tests. Alternatively, continuous variables that did not follow a normal distribution are presented as medians (interquartile ranges), and group comparisons were performed using the Wilcoxon test. Categorical variables are reported as frequencies (percentages), and group differences were evaluated using either the chi-square test or Fisher's exact probability method. Statistical significance was considered when  $P < 0.05$ .

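### Comparability of the matched groups rests only on non-significant baseline tests, which at 68 per group cannot show balance; the main exposure is the unmatched, unadjusted admission values of the outcomes

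*Combined protocol and SAP*

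**What the plan says.** All places are in the combined protocol and SAP.

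- **Allocation.** Under Randomization, "the participants were not randomly assigned". Study Design states that the groups were formed by admission date: control April to May 2022, intervention May to June 2022.
- **Purpose of matching.** Study Design describes "propensity score matching to balance the baseline characteristics between the two groups, ensuring comparability". Randomization says that nearest-neighbour 1:1 matching was used "to ensure balanced characteristics between the intervention and control groups". It gives a calliper of 0.2 without a scale.
- **Matching covariates.** Randomization names 13, introduced as examples: age, sex, education, marital status, exercise habits, salary, address, living alone, history of CHD, history of PCI, length of stay, insurance and polypharmacy. Admission 6MWT, SF-12, frailty, fitness measures and lipids are not named.
- **Size.** 164 patients (89 and 75) were reduced to 136, "with 68 patients in the multidimensional digital cardiac rehabilitation group and 68 patients in the usual care group".
- **Evidence of balance.** Results: "Statistically, non-significant differences were observed between the two groups after matching baseline data", with P ≥ 0.05.
- **Tests.** Statistical Method: for continuous variables "differences between groups were assessed via t tests" (Wilcoxon if not normal), and for categorical variables "group differences were evaluated using either the chi-square test or Fisher's exact probability method", at the 0.05 level. No covariate adjustment is described.

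The text contains no standardised mean difference (SMD), variance ratio or balance margin.

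**The concern.** Without randomisation, a causal reading of the outcome differences depends on the matched groups being alike. A non-significant test does not establish that. It means only that the data could not rule out zero difference, and with small groups they also cannot rule out differences large enough to confound. A P-value also depends on sample size, and matching discards 28 patients, so a baseline P-value can rise with no improvement in balance.

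What is at stake is any imbalance that goes unseen and is not then removed in the analysis. The admission value is usually among the strongest predictors of the same measure three months later. It is neither a listed matching covariate nor a term in the described outcome tests, so an imbalance there would carry into the three-month group differences.

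**Working it through.** The documents give no power, sample-size or balance figure, so there is nothing to reproduce first. The stated counts do agree with each other: 89 + 75 = 164, 68 + 68 = 136, 59/136 = 43.38%.

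**Inputs.** n = 68 per group (Randomization); alpha 0.05 (Statistical Method), taken as two-sided because sidedness is not stated; independent-sample tests, because no paired analysis is described. The imbalance sizes of interest are assumptions, so a range is shown.

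**1. Largest observed difference that still gives P > 0.05.** Limit = t(0.975, df) × √(1/n₁ + 1/n₂).
- After matching: t(0.975, 134) × √(2/68) = **0.339 SD**.
- Before matching, 89 vs 75: **0.310 SD**.

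This needs no assumption about the true imbalance. An unchanged observed difference of 0.325 SD has P = 0.040 at 89 vs 75 and P = 0.060 at 68 vs 68. The window in which such relabelling can happen is narrow (0.310 to 0.339), so this is a secondary point.

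**2. Chance of missing a true imbalance d.** Miss rate = P(|T| ≤ t(0.975, 134)), where T is noncentral t with 134 df and noncentrality d/√(2/68) = 5.831 d.

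| True imbalance (SD) | Noncentrality | Miss rate |
|---|---|---|
| 0.10 | 0.583 | 91.1% |
| 0.15 | 0.875 | 86.0% |
| 0.20 | 1.166 | 78.8% |
| 0.25 | 1.458 | 69.6% |
| 0.30 | 1.749 | 58.8% |
| 0.40 | 2.332 | 36.1% |
| 0.50 | 2.915 | 17.5% |

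A binary covariate behaves the same way: 43% vs 48% (SMD 0.10) is missed 91.6% of the time, and 43% vs 55.5% (SMD 0.25) 69.4%. By the normal approximation, 80% power would need 1,570 per group for 0.10 SD and 252 per group for 0.25 SD.

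**3. What the reported result would allow.** The documents give 59 women among 136 but no split by group. A hypothetical split of 24/68 vs 35/68 (35% vs 51%) gives a chi-square P of 0.057, or 0.084 with continuity correction. The SMD is (0.515 − 0.353)/√[(0.353 × 0.647 + 0.515 × 0.485)/2] = 0.33. A gap of 16 percentage points would therefore fit the sentence in Results. The split is illustrative only.

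**4. Which admission values exist.** Physical Fitness records grip strength and walking speed at admission and three months, and Blood lipid indices does the same for lipids. The 6MWT, SF-12 and frailty sections state no admission measurement. Section 1.1 (Exercise Training) refers to a 6MWT used to set exercise intensity, but only for the intervention group. For the three primary outcomes, then, the text does not establish that an admission value exists in both groups.

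**The case against.** **Matching constrains the covariates it uses.** The miss rates treat the imbalance as fixed and unconstrained, whereas a propensity score built from the 13 covariates and matched within a calliper pulls them together. Simulations of 89 vs 75 with 13 independent normal covariates (an assumption) and greedy calliper matching bear this out. A given covariate ended more than 0.25 SD apart in about 1% of runs or fewer, and two covariates both off by 0.3 SD or more in the same direction never occurred. This stands. A reader might turn an imbalance of 0.25 to 0.33 SD, with assumed outcome correlations of 0.3 to 0.5, into a false-positive rate of 7% to 16%, or about 28% for two covariates. For the matched covariates those figures are not supported and should not be used. They also treat 0.33 SD, close to the largest non-significant observed difference, as a true one.

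The reassurance has limits. The calliper bounds distance on the score and not on each covariate, its scale is not given, and it does not act directly on variables left out of the score. In some of those simulations at least one of the 13 still exceeded 0.25 SD in 5% to 12% of runs.

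**There is no stated balance rule.** A reader might infer that the plan makes P ≥ 0.05 a formal criterion for comparability. It does not: the sentence in Results reports a finding, and the wording in Study Design and Randomization states the purpose of matching. That stands, but the P-values remain the only support offered.

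**The outcome analysis may account for baseline.** The Discussion speaks of time effects, which suggests a longitudinal analysis. Statistical Method describes none, so this is unclear and cannot be credited.

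**An SMD limit of 0.10 is too strict as a trigger.** This stands. At 68 per group a perfectly randomised covariate exceeds 0.10 with probability P(|Z| > 0.10 × 5.831 = 0.583), or 56%. The 0.10 value can only describe.

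**Conclusion.** The point holds in a limited form: balance after matching is not demonstrated. The 0.34 SD limit follows directly from the test and the group size, assuming a two-sided independent-sample t test. The 91% to 70% miss rates rest additionally on the assumed range of 0.10 to 0.25 SD, and the point weakens for imbalances of 0.5 SD or more.

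For the 13 listed covariates, large residual imbalance is unlikely, though not shown to be absent. The more serious gap concerns the admission values of the outcomes, for which the documents describe neither matching nor adjustment. The covariate list is given as examples, so such values may have been used without being named; the text does not say so.

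A reader might also conclude that the groups are in fact imbalanced, or that the reported effects are due to confounding. Nothing in the documents shows either, and no size of bias can be derived from them.

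**What to change.** - **Randomization and Results.** Replace the P-value evidence with SMDs before and after matching for every matching covariate and every available admission outcome value. Show 0.10 as a descriptive reference, not as a trigger for re-specifying the score or choosing adjusters. State the calliper's scale and the full covariate list.
- **Statistical Method.** Compare each outcome with a regression that always includes the admission value of that outcome where it was recorded. Add a sensitivity analysis that also includes the matching covariates. Fixing the terms this way means that they are not chosen by observed imbalance.
- **Primary outcomes.** State whether 6MWT, SF-12 and frailty were measured at admission in both groups. If not, say that balance on them cannot be shown.
- **Study Design.** Reword the comparability claim to say that matching was intended to improve comparability, and report the largest residual SMD.

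The cost is small and uses data already collected: SMD columns in the baseline table and one extra term per main model. If each matching covariate takes one term, the sensitivity model leaves 136 − 2 − 1 − 13 = 120 residual degrees of freedom, and fewer with multi-category covariates. The stated balance may look less favourable than it does now.

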## Discussion

Findings indicated that a multidimensional digital CR intervention improved functional status (FP, 6MWT, gait speed, and 30-s CST) and metabolic markers (TC, TG, and LDL-C) in patients with UA undergoing PCI within a relatively short period compared to standard management. These results emphasize the program's potential to enhance physical recovery and cardiovascular health. Significant time effects were also observed for grip strength, WC, BMI, and overall quality of life (physical and mental components), reinforcing the efficacy of digital interventions. This novel rehabilitation model provides CVD education, clarifies essential diagnostic procedures, provides exercise rehabilitation guidance, and supports home-based rehabilitation. Promoting physical activity, encouraging lifestyle modifications, and facilitating behavioral changes during recovery contribute to improved quality of life in patients with UA undergoing PCI.

## **Informed Consent**

Multidimensional digital cardiac rehabilitation research trials of recruiting, screening, and into the group of participants in the First Hospital of Bengbu Medical University. We through the electronic system of the hospital and outpatient clinic to determine potential qualified patients, and arrange the next recruitment consultancy. We consulted all potential patients who met the major inclusion criteria on-site at the time of admission. In the process of participants selected, willing to participate in trials of patients will be required to allow to input the information into the database, for the next step screening of patients. Patients is expected at the beginning of the screening visit to conduct a comprehensive screening, to evaluate the qualification test. Patients who pass the screening visit will be considered eligible to enter the informed consent process. During this process, we will provide eligible patients with a detailed verbal description of the study, including its risks, potential benefits, and requirements. We will also provide a paper informed consent form for eligible patients to read, and patients will have ample time to read and reflect on participation. If required, the individual will be given additional time to consider participation, including rearranging the screening visit. Before get written consent, everyone can ask questions, until individual decision making. When ready, participants will be asked to sign the consent form. Then, we will collect the data to provide informed consent of patients, including from the eligible patients' electronic health records and research the information of the program.
